### Subject withdrawal

Patients may withdraw from the study at several stages of the trial, if they wish it, even after having signed the Consent Form. They may also reject an intervention or reject a follow-up evaluation. If patients reject the operation, then they will be excluded from the study. If they reject a follow-up evaluation, then their data will be analyzed and individually reported at the final report of this trial, irrespective of their group. During surgery, if moderate or severe rotator cuff arthropathy is found, or if the surgeon fails to repair the cuff or release the SSN, then patients will be withdrawn from the trial. Postoperatively, patients may be removed from the RCT if they deteriorate and a diagnosis of rotator cuff re-rupture is made by ultrasound or MRI studies.

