### Study procedure

Patients will be randomized on the admission day and allocated to a group, so that they may undergo arthroscopic rotator cuff repair alone, or combined with arthroscopic release of the SSN. Only the operating surgeon, who will be the same for all patients, will be aware of the randomization results and patient allocation list.

All patients are going to be treated according to the established institutional protocol and the operation will follow well-defined standards in order to minimize adverse factors. All operations will be done with the patient in a beach-chair position, under general anesthesia and with a regional (interscalene) anesthetic block for postoperative analgesia. If general anesthesia is contraindicated, then the procedure will be done with the patient awake or mildly sedated and with the regional block as the main anesthetic agent; these patients will be recorded. Prepping will be done as per hospital protocol with aqueous povidone iodine 7.5%, and draping will be the same for all patients. Standard portals will be made for all patients: posterior, anterior, lateral, and anterolateral; a superior portal will additionally be made for patients undergoing release of the superior transverse scapular ligament.

The procedure will aim at fully restoring the rotator cuff to its anatomical footprint. When the cuff is not repairable then these patients will be excluded from the study. If during the operation the surgeon fails to fully repair the cuff and achieves only a partial repair, these patients will be recorded and followed up but separated from the cohort; their outcomes will be compared with those of the rest. All repairs will be done using a transosseous equivalent technique with peek anchors, knotted medially and knotless laterally. Arthroscopic release will follow the technique published by Lafosse et al. [1]. Visualization will be done mostly by the lateral portal and the shaver will mostly work through a lateral-anterolateral portal. The transverse ligament will be dissected via a superior portal, which is created under direct vision and uses a needle to identify the exact location of the portal.

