### Trial duration

The main trial period will start 6 weeks prior to surgery (where clinical NC/EMG and MRI evaluation will be done) and will include the operative intervention and the postoperative period up to the last follow-up. Follow-up clinical examinations and NC/EMG studies for all patients will be conducted at 6 and 12 months after surgery. MRI studies for each patient will be done at least 1 year after the date of the operation.

With a recruitment period of 24 months and a follow-up period of 12 months, the total length of this study is expected to be approximately 36 months. This trial will end when all the necessary 42 patients have completed it. Also, the principal investigators may decide to terminate the study at any time for any reasonable or medical reasons. The final report of this trial will follow the CONSORT guidelines and its extension for nonpharmacological interventions.

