### Statistics

#### Sample size calculation

Statistical analysis of previous relevant medical literature was used in order to identify the number of patients needed for this trial. Since no similar studies could be found, we searched for results from similar articles relative to the trial. Costouros et al. [7] treated six patients with massive rotator cuff tears and SSN neuropathy by arthroscopically repairing the cuff. They found complete nerve recovery in four out of six patients. Oizumi et al. [17] performed an arthroscopic release in 18 patients with a rotator cuff tear and all had complete recovery from SSN palsy, although the diagnosis was clinical and no NC/EMG studies were done. Lafosse et al. [1] mention unpublished data of 29 massive rotator cuff tear cases accompanied by SSN neuropathy, where no statistical difference was found between patients who underwent nerve release and patients who did not; however, no further data or tables are provided and the cases are anecdotal. Therefore, we considered that 100% of patients undergoing nerve release and 66.67% of patients undergoing rotator cuff repair only could have full nerve recovery.

We used the statistical program G*Power [18] in order to do a priori power analysis of the primary endpoint of this study. By using a Fisher’s exact test to compute differences between these groups, a 100% success probability of the first group (nerve release) and a 66.67% probability of the second group, a error probability set at 0.05, power set at 0.8, and an allocation ratio equal to 1, a total of 38 patients were found to be needed, 19 for each group. Usually, patients who undergo such operations rarely miss standard follow-ups in this institution because these are part of their physiotherapy and clinical postoperative care (apart from the NC/EMG studies). If 10% of recruited patients fail to attend follow-ups for any reason, then 42 patients will be required for this RCT.

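### Withdrawing failed releases (possible in one arm only) and deteriorating re-ruptures after randomisation leaves the primary comparison on a selected set

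*Protocol article*

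**What the plan says.** Randomisation precedes surgery: Study procedure places it on the admission day, and Randomization/blinding assigns consecutive list cells at recruitment. Several later events then take patients out.

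- **Failed repair or failed release.** Subject withdrawal: if the surgeon "fails to repair the cuff or release the SSN, then patients will be withdrawn from the trial". Moderate or severe arthropathy found at surgery has the same consequence.
- **Re-rupture.** Same section: "patients may be removed from the RCT if they deteriorate and a diagnosis of rotator cuff re-rupture is made" by ultrasound or MRI. No decision-maker or time limit is given.
- **Partial repair.** Study procedure: "these patients will be recorded and followed up but separated from the cohort", with their outcomes compared with those of the rest.
- **Refused follow-up.** Subject withdrawal: the data are to be analysed and "individually reported at the final report of this trial, irrespective of their group".

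Statistical methods names Fisher's exact test for the primary endpoint and no analysis set. Sample size calculation allows for missed visits only: "If 10% of recruited patients fail to attend follow-ups for any reason, then 42 patients will be required for this RCT". Trial duration says: "This trial will end when all the necessary 42 patients have completed it".

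**The concern.** Randomisation makes the arms comparable as allocated. Two of the rules break this in ways that can bear on the primary endpoint.

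Failed release cannot occur in the repair-only arm. Withdrawing it removes technical failures from the release arm and leaves the control arm whole. If these patients recover less often than the rest of their arm, release looks better than it is.

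Re-rupture removal is optional and requires deterioration. The Discussion argues that restoring the tendon is what frees the nerve, so on the plan's own reasoning a failed repair bears on nerve recovery. The MRI is scheduled at 12 months or later, so a re-rupture may be diagnosed with or after the last nerve study, when the outcome is already known. The bias could go either way, depending on how removals fall between the arms.

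Withdrawal also governs data collection. Follow-up is promised for partial repairs but not for failed releases or re-ruptures, and outcomes that were never collected cannot be restored at analysis.

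**Working it through.** **Inputs from Sample size calculation.** Full recovery 100% (release) and 66.67% (repair only); "a error probability set at 0.05, power set at 0.8, and an allocation ratio equal to 1"; 19 per arm, then 42 in all (21 per arm). The test is a Fisher's "exact test to compute differences between these groups". Sidedness is not stated; two-sided is used here.

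**1. The plan's own figure.** At 19 per arm with 19/19 in the release arm, 14/19 in the control arm gives two-sided p = 2 × C(19,5)/C(38,5) = 2 × 11,628/501,942 = 0.046. Power is therefore the probability of at most 14 recoveries among 19 at 2/3, which is 0.812. At 18 per arm power is 0.769. So 19 per arm reproduces, and 38 × 1.10 = 41.8 gives 42. The sample-size arithmetic is not the fault.

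**2. How few removals decide the result** (assumed counts).

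| Release | Control | Two-sided p |
|---|---|---|
| 18/21 | 14/21 | 0.28 |
| 18/18 (three non-recovered dropped) | 14/21 | 0.010 |
| 19/21 | 14/21 | 0.13 |
| 19/19 (two non-recovered dropped) | 14/21 | 0.009 |

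For 18/18 against 14/21 there are 39 patients and 7 non-recoveries, all in the control arm: p = [C(21,7) + C(18,7)]/C(39,7) = (116,280 + 31,824)/15,380,937 = 0.0096.

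**3. Error rate with no true difference.** Let recovery be 2/3 in both arms, 21 each. For every pair (a, b) of recovery counts, drop the smaller of k and 21 − a non-recovered patients from the release arm, apply Fisher's test, and sum the binomial probabilities of the pairs with p ≤ 0.05.

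| k dropped, release arm only | Rejection rate |
|---|---|
| 0 | 0.022 |
| 2 | 0.076 |
| 3 | 0.127 |

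A milder model treats the retained patients as a fresh binomial sample at the shifted rate. Dropping 2 or 3 then gives 14/19 = 73.7% or 14/18 = 77.8%, apparent gains of 7 and 11 points over 66.7%, and rejection rates of 0.057 and 0.091. If a third of the dropped patients had in fact recovered, that model gives 0.040 and 0.046. With four non-recovered patients removed from each arm the difference is zero and the rate is 0.018. The damage comes from removal that is unequal between arms and related to outcome.

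**4. Numbers.** The margin is 42 − 38 = 4 patients, two per arm, all set aside for missed visits. If missed visits use it up and two more per arm are excluded at surgery, 17 per arm remain and power is 0.72.

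**The case against.** The strongest objection is that the article names no analysis set, and a separate analysis plan may specify all randomised patients. That is fair as far as it goes, and the absence of a named set is not the complaint. But the rules as written take patients out of the trial and promise no outcome collection, so an all-randomised analysis would contradict them and would lack the data.

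Several stronger readings are tempting and not supported.

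- **That every exclusion at surgery selects by arm.** Randomization/blinding has the envelope opened just after the cuff repair is finished. Failed repair, partial repair and arthropathy are thus found before the arm is revealed and should not differ by arm. This holds only if the surgeon does not know the allocation. Study procedure says the surgeon knows the allocation list, and Randomization/blinding also has the surgeon informed on the admission day.
- **That partial repair is plainly contradicted.** Study procedure speaks of failing to repair fully, Subject withdrawal of failing to repair. The second may mean only the irreparable cuff. The wording is ambiguous.
- **That patients refusing follow-up are certainly outside the comparison.** The sentence also says their data will be analysed. It is unclear.
- **That all 42 must have complete data.** The wording on the trial's end is loose and does not bias the comparison.
- **That re-rupture removal causes a stated loss of power.** The documents give no re-rupture rate. Suppose 20–25% re-rupture, 30% of those recover, and all are removed. The control rate becomes (0.667 − 0.20 × 0.30)/0.80 = 0.758 or (0.667 − 0.25 × 0.30)/0.75 = 0.789. With 17 or 16 per arm and release held at 100%, power is about 0.39 or 0.24. Keeping everyone puts release at 1 − 0.20 × 0.70 = 0.86 or 1 − 0.25 × 0.70 = 0.825, and power at 0.21 or 0.13. The loss cannot be blamed on the removal.

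It also stands that the counts in the working are illustrative. A biased estimate need not be a false positive: 14/19 or 14/18 against 14/21 gives p = 0.74 or 0.50.

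**Conclusion.** The point holds for two rules: withdrawal for failed release, which selects by arm, and discretionary removal of deteriorating re-ruptures, which selects by clinical course. Followed as written, they put the primary comparison on a set that randomisation no longer protects.

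The size depends on counts that the article does not give. Under the assumptions shown, two or three one-sided removals of non-recovered patients can move p from 0.13 or 0.28 to about 0.01. They can raise the two-sided error rate from 0.022 to 0.076–0.127 (0.057–0.091 under the milder model). If some removed patients had recovered, the inflation is smaller and may stay under 0.05. Failed-release removal favours release when failures recover less often; the direction for re-rupture is open.

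The exclusions found before the envelope is opened are a matter of numbers rather than arm-related bias, provided the surgeon does not know the allocation. Partial repair, refused follow-up and the end of the trial need clearer wording only. This should be corrected while the trial is recruiting, since outcomes not collected cannot be recovered later.

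**What to change.** 1. For the primary endpoint, analyse every randomised and operated patient in the allocated arm, including failed releases and re-ruptures.
2. Keep these patients in the nerve conduction and EMG assessments already scheduled at 6 and 12 months.
3. Present the Subject withdrawal exclusions only as a secondary per-protocol analysis.
4. Report cases excluded before the envelope is opened separately, by allocated arm. Reconcile Study procedure with Randomization/blinding on what the surgeon knows and when.
5. Reconcile Study procedure, Subject withdrawal and Trial duration on partial repair, refused follow-up and when the trial ends.
6. Examine missing 12-month results with best-case and worst-case sensitivity analyses. Counting missing as not recovered should not be imposed as the primary rule: with two missing per arm, power falls from 0.81 (19 complete per arm) to about 0.46.

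**Cost.** Protocol wording, plus visits already scheduled. The release-arm recovery rate may look less favourable, and power falls if releases fail. Suppose 1, 2, 3 or 4 of 21 releases fail and those patients recover at 2/3, so that the release rate is [(21 − k) + k × 2/3]/21. Power with 21 per arm is then 0.78, 0.68, 0.59 or 0.50, against 0.88 with none. Withdrawing them would show 0.88, 0.88, 0.75 or 0.75, but for a comparison that leaves out the failures. If failures are expected, the sample size should be revisited.

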## Discussion

Published studies have demonstrated a relation between SSN neuropathy and large/massive retracted rotator cuff tears [8, 9]. Mallon et al. analyzed the outcomes of eight patients with SSN neuropathy and a massive retracted rotator cuff tear. All these patients also presented with SSN neuropathy that was confirmed by EMG studies. Four of these patients underwent partial repair of the cuff. Two of them showed re-innervation potentials [8]. In the Shi et al. study, 87 patients underwent NC/EMG studies and MRI of their symptomatic shoulder. The study concluded that an exact relation between SSN neuropathy and rotator cuff pathology remains unclear and found that SSN neuropathy is associated with tendon tear size. However, this relation was not linear as minimally retracted tears were more strongly correlated with SSN neuropathy when compared to bigger ones. This study aims to better define that relationship and to discover the most effective treatment for this disease. If both interventions performed in this trial have the same potential in reversing SSN neuropathy, then there will be no need to release the SSN when dealing with SSN neuropathy in the setting of large/massive rotator cuff tears. Just by repairing the tendon and, therefore, the length of the muscle/tendon unit, the nerve will be freed and have potential for re-innervation.

Experimental studies have revealed a possible relation between the size of rotator cuff tear and degree of nerve damage. Warner et al., in their cadaveric study, determined that lateral reduction of rotator cuff tears of more than 3 cm might result in significant tension on the SSN and entrapment as the nerve passes through the transverse scapular ligament [19]. Greiner et al., in another cadaveric study, found that that the maximum lateral advancement of a retracted rotator cuff tear is between 1 and 3 cm. As advancement progresses, the neurovascular pedicle is placed under increased tension [20]. However, Hoellrich et al. did EMG studies and did not find any SSN neuropathy after repairs of massive rotator cuff tears in nine patients (mean advancement of 2.5 cm, range 2.0 to 3.5 cm). They concluded that the tendons could be mobilized and advanced up to 3.5 cm without putting the SSN at risk [21]. Although studies suggest nerve damage even after small traction, the medical literature has shifted towards finding a relation between SSN neuropathy and massive rotator cuff tears (more than a 5-cm tendon gap).

Electromyography studies are generally considered in patients with unexplained shoulder pain, but his has been debated as authors disagree about the sensitivity and specificity of EMG [22–24]. A damaged nerve can produce several abnormal findings on an EMG, such as reduced amplitude of motor potentials, increased spontaneous activity, fibrillations, polyphasic activity, and fibrillation and sharp waves. The accuracy of NC/EMG studies in assessing SSN neuropathy has been challenged, as there are no clear criteria [12]. Diagnosing SSN neuropathy in patients with massive rotator cuff tears can be even more difficult, especially clinically, as the symptoms between these entities overlap. Due to the lack of any other validated foolproof test, however, NC/EMG studies have become the “gold standard” [12].

It has been impossible so far to validate NC/EMG studies in patients with rotator cuff tears. Muscle biopsy or neural cell adhesion molecule histochemistry can indicate denervated muscle as shown in experimental models. However, its accuracy fails in the setting of a tenotomized muscle [25], which also affects EMG studies [26]. Thus, no trials have previously validated NC/EMG studies for the diagnosis of SSN neuropathy in the setting of large/massive rotator cuff tear, nor have they defined concise diagnostic criteria. Colin et al., in an attempt to define the prevalence of suprascapular neuropathy with repairable massive rotator cuff tears in 49 patients below 65 years of age, documented the diagnostic criteria that they used when performing NC/EMG studies [12]. Interestingly, they found a low relation (2%) between SSN neuropathy and massive rotator cuff tears.

Techniques used in order to perform SSN release can be open or arthroscopic. Open SSN release has provided good results in a series of 39 patients; 28 showed improvement of supraspinatus muscle strength to grade 4 [11]. However, arthroscopic techniques have gained momentum, possibly due to being less invasive, having better visualization and having the ability to be combined with repair of the rotator cuff without the need for extra incisions.

The technique of arthroscopic transverse scapular ligament dissection has been described previously [1, 27–29]. Lafosse et al. in 2007 reported excellent outcomes in nine out of ten patients who underwent SSN arthroscopic decompression without rotator cuff repair [28]. Complete normalization of latency in NC/EMG studies was found in seven of these patients. Costouros et al. reported six patients with SSN neuropathy related to massive cuff tear. He found complete improvement in EMG function in four and partial recovery in two patients [7]. In a study by Shah et al., 21/24 (87.5%) patients had deep posterior shoulder pain and NC/EMG findings of SSN denervation. After SSN decompression, 17/24 (71%) of these patients had reduced levels of pain at 9 weeks after surgery and demonstrated improved ASES scores [30]. The authors also hypothesized that there may be a subgroup of patients with negative NC/EMG studies presenting with unexplained posterior shoulder pain and that these patients may respond to SSN decompression.

The studies above show promising results after release of the SSN, but reversal of muscle atrophy is not always observed. Kim et al. reported 90% of patients with profound muscle weakness regaining supraspinatus muscle strength to grade 4 or better, but infraspinatus muscle strength gains were less predictable [11]. Fabre et al. reported 89% of patients obtaining good-to-excellent outcome after open SSN decompression, but reversal of muscle atrophy was only seen in half of these patients (52%) [31].

In conclusion, published studies so far deliver some evidence regarding the relation between SSN and massive cuff tears and suggest good/excellent postoperative outcomes, with or without releasing the SSN. These cohort studies provide ultimately inconsistent and ambivalent results, as they do not measure their current management with an alternate treatment. The need for comparable studies becomes apparent in order to create a guideline, which would assist shoulder surgeons in making effective and safe treatment choices when dealing with patients with repairable large/massive rotator cuff tears and SSN neuropathy.

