We searched the websites of online trial registries, “http://www.clinicaltrials.gov/,” “http://www.isrctn.com,” “http://onlinelibrary.wiley.com/cochranelibrary,” as well as “http://www.ncbi.nlm.nih.gov/pubmed.” To the best of our knowledge, there are no randomized prospective studies that compare the outcome of SSN neuropathy after arthroscopic dissection of the transverse scapular ligament in patients with a torn rotator cuff against control groups that did not undergo ligament dissection. We are also unaware of any studies that aimed to find any relation between the degree of neuropathy and the size of the rotator cuff tear. The primary objective is to test the null hypothesis that arthroscopic repair of large/massive rotator cuff tears in patients with combined suprascapular neuropathy provides equivalent outcomes to one-stage arthroscopic cuff repair where the superior suprascapular ligament is additionally released. The secondary objective is to search for a relation between rotator cuff tear size and degree of SSN recovery. The tertiary objective is to demonstrate any relation between rotator cuff muscle fatty infiltration grade and degree of SSN function.

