#### Statistical methods

Statistical analysis will be carried out after all patients have completed 12 months of follow-up. Fisher’s exact test will be used for the primary endpoint of the trial. In order to analyze secondary endpoints, the type of data distribution will be studied. If the results follow a normal distribution, the chi-square test and *t* test will be used to compare qualitative and quantitative parameters accordingly. If the results do not follow a normal distribution, quantitative parameters will be studied with the Mann-Whitney test. Depending on the data collected, further tests, such as the Wilcoxon and Kruskal-Wallis tests, may be done for subgroups. Statistical differences will be considered significant if *P* < 0.05.

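### The trial is built and analysed only to detect a difference, yet the article foresees concluding that release is unnecessary if the arms perform the same, with no margin or interval rule to support that.

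*Protocol article*

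**What the plan says.** Four parts of the protocol article bear on this.

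- **Objective** (Abstract, and end of Background). The primary aim is to "test the null hypothesis that arthroscopic repair of large/massive rotator cuff tears in patients with combined suprascapular neuropathy provides equivalent outcomes" to those of repair with added release of the ligament.
- **Sample size calculation.** The inputs are "a 100% success probability of the first group (nerve release) and a 66.67% probability of the second group", with an error probability of 0.05, power of 0.8 and 1:1 allocation. The result is 38 evaluable patients (19 per arm), raised to 42 for 10% loss to follow-up.
- **Statistical methods.** "Fisher’s exact test will be used for the primary endpoint of the trial". The threshold is P < 0.05.
- **Discussion**, first paragraph. "If both interventions performed in this trial have the same potential in reversing SSN neuropathy, then there will be no need to release the SSN" in patients with these tears.

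The article gives no equivalence or non-inferiority margin and no rule by which the two procedures would be judged to have the same potential. It also gives no minimum important difference.

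**The concern.** The objective speaks of equivalent outcomes and the Discussion looks ahead to a conclusion of sameness. The sample size and the test address only whether the arms differ. A difference test that fails to reject leaves the question open, because the data may fit both no benefit and a substantial benefit of release. If the trial ends without significance, the only primary result available would be a P value above 0.05. The Discussion's sentence invites the reader to take that as evidence against a surgical step. The article's closing argument is that comparative studies are needed to build a guideline, so an unsupported claim of sameness could influence practice.

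**Working it through.** **Inputs.** From Sample size calculation: 100% against 66.67%, alpha 0.05, power 0.8, 19 per arm, 42 recruited (21 per arm). From Statistical methods: Fisher's exact test, P < 0.05. The article does not state whether the test is one- or two-sided; two-sided is used here. The other recovery rates and all margins below are assumptions.

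**1. The plan's own figure.** If release succeeds in every patient, all 19 recover. Fisher's test gives p = 0.046 for 19/19 against 14/19 and p = 0.105 for 19/19 against 15/19, so the result is significant when 14 or fewer control patients recover. Power is therefore P(X ≤ 14) with X ~ Bin(19, 2/3), which is 0.812. With 18 per arm it is 0.769. Nineteen per arm is the first size above 0.80, so the stated 38 reproduces.

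**2. Power at smaller effects.** This is the exact sum, over all outcome pairs with p ≤ 0.05, of the product of the two binomial probabilities. For 100% against 80%, for example, it is P(X ≤ 14) with X ~ Bin(19, 0.8), which is 0.327.

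| True recovery, release vs repair only | 19 per arm | 21 per arm |
|---|---|---|
| 100% vs 66.67% (design) | 0.81 | 0.88 |
| 100% vs 75% | 0.53 | 0.63 |
| 95% vs 66.7% | 0.51 | 0.57 |
| 100% vs 80% | 0.33 | 0.41 |
| 90% vs 66.7% | 0.30 | 0.34 |
| 86.7% vs 66.7% | 0.20 | 0.23 |

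In the two 20-point scenarios with 19 per arm, the test would miss the benefit 67% (1 − 0.33) to 80% (1 − 0.20) of the time.

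**3. What a null result leaves open.** The Newcombe interval for d = p1 − p2 uses the Wilson limits (l, u) of each arm:

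- lower limit = d − √[(p1 − l1)² + (u2 − p2)²]
- upper limit = d + √[(u1 − p1)² + (p2 − l2)²]

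For 13/19 in both arms, p = 0.684 and the Wilson limits are 0.460 and 0.846. The half-width is √(0.224² + 0.162²) = 0.277.

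| Observed, release vs repair only | Fisher p | Difference (points) | 95% interval (points) |
|---|---|---|---|
| 13/19 vs 13/19 | 1.00 | 0 | −28 to +28 |
| 16/19 vs 16/19 | 1.00 | 0 | −24 to +24 |
| 19/19 vs 19/19 | 1.00 | 0 | −17 to +17 |
| 18/19 vs 14/19 | 0.18 | 21 | −3 to +44 |
| 18/19 vs 13/19 | 0.09 | 26 | +1 to +49 |

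**4. Size needed to show sameness (illustration).** For non-inferiority of repair alone at a common rate p and margin m, n per arm = 2p(1 − p)(1.960 + 0.842)² / m², with one-sided alpha 0.025 and power 0.80. At p = 0.833 and m = 0.20, 2 × 0.833 × 0.167 × 7.85 / 0.04 = 54.5, so 55 per arm or 110 in total. Over margins of 10 to 20 points and common rates of 66.7% to 90%, the total runs from 72 (90%, 20 points) to 698 (66.7%, 10 points), against 38 planned. A margin as wide as the full 33.3-point design effect would need 26 (at 90%), 40 (at 83.3%) or 64 (at 66.7%).

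**The case against.** Much of the opposing case stands.

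- **The null hypothesis is not an error.** In a formal equivalence trial, equivalence is the alternative. Naming it as the null is loose wording for the ordinary no-difference null, which Fisher's test addresses. A reader might infer that the hypothesis or the sample size is wrong. Neither is, for superiority.
- **The Discussion sentence is conditional.** It concerns what the procedures truly do, and mentions neither Fisher's test nor P ≥ 0.05. A reader might infer that the plan commits to reporting a non-significant result as proof that release is unnecessary. No section says so. What remains is that no other route to a finding of sameness is offered.
- **Missing significance is not the expected result under the plan's own assumptions.** At the design effect the test succeeds 81% of the time with 19 per arm, and 88% if all 42 are analysed. A reader might infer that the trial will probably miss any clinically large benefit. That holds only for effects well below the assumed one, and the article does not say what size of benefit counts as large.
- **An unmentioned confidence interval is no fault in itself.** A condensed article may leave it to a fuller document, and this one commits the final report to CONSORT. The interval matters here only because the sameness conclusion has nothing else to rest on.

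**Conclusion.** The concern holds in limited form. The design, sample size and test are sound for superiority at a 33-point effect. They do not support the no-need-to-release conclusion that the Discussion foresees, and the article gives no margin or interval rule that would. Even identical observed rates would leave benefits of roughly 24 to 28 points within the 95% interval at 16/19 or 13/19 per arm. A true 20-point benefit would be missed in about two-thirds to four-fifths of trials with 19 per arm, or 59% to 77% with all 42 analysed (1 − 0.41 and 1 − 0.23).

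These figures assume two-sided testing, Newcombe intervals and the illustrative rates shown. The 20-point effect and the margins are assumptions, not values from the article. Because the remedy is one of wording and the primary test is unaffected, this is should-fix.

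**What to change.** 1. **Abstract and Background, primary objective.** Replace the phrase about equivalent outcomes with a null of no difference in the probability of full nerve recovery, the quantity used for the sample size.
2. **Statistical methods.** Keep Fisher's test. Add that interpretation rests on the risk difference with its 95% confidence interval, and that a non-significant result is inconclusive. Name the interval method, since it can disagree with Fisher's test near the boundary: 18/19 against 13/19 gives p = 0.09 but a Newcombe interval that just excludes zero.
3. **Discussion.** Allow the no-need-to-release conclusion only if the upper confidence limit for the benefit of release lies below a margin that the sponsor justifies and fixes before unblinding. Add that about 38 evaluable patients are unlikely to meet a narrow margin.

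**Cost.** Three changes of wording, with no new patients and no change to treatment or to the primary test. A null result would then support a weaker claim. If the sponsor wants to demonstrate sameness, a margin alone will not be enough unless it is very wide, and the trial would have to be resized.
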